#### Recruitment via postal survey

A random selection of 5000 residents (n = 2500 from each park area) who lived within a 5 km buffer of the two parks were identified from the two City Councils within which the parks were located. Pre-notification postcards were sent from the Council mail room to all residents one week prior to the survey being posted. A survey addressed ‘to the resident’ was then posted to each resident in a Council envelope with a letter from the Council inviting their participation in the study, a plain language statement, a consent form and a reply-paid envelope for survey return. In order to encourage survey return, follow-up reminder postcards were posted to all residents two weeks and six weeks after they received the survey.

#### Survey

The 91 item self-report survey was designed to include measures of the outcome variables (park usage, physical activity and active travel), potential determinants of these outcomes and relevant covariates. Respondents with a child(ren) aged 2–15 years living in the household, were asked to consider the child in the age range who had the next birthday and complete additional proxy-report survey questions regarding that child’s use of parks and related behaviours.

A socio-ecological framework [34] was used to develop the survey instrument which measured all three levels of influence on behaviours (intrapersonal, social and neighbourhood environmental influences). The survey included socio-demographic variables (age, sex, country of birth, marital status, employment status, highest level of education, motor vehicle access, dog ownership, time spent living at residential address and in the neighbourhood, and number of children) and participants self-reported their weight and height.

Where possible, established survey items from the literature with known reliability and validity were used. Self-reported transportation and leisure-time physical activity and time spent sitting in the last seven days was examined using the long form of the International physical activity questionnaire (IPAQ-L) [35]. Four items examined self-reported stress [36], ten items examined self-reported depression. CES-D10 [37] and a single item examined self-reported general health using the Short Form Health Survey (SF-36) (http://www.rand.org/health/surveys_tools/mos/mos_core_36item.html).

Nine existing items assessed perceptions of neighbourhood safety, violence, crime, attractiveness, opportunities to be active and walkability [38]: I feel safe walking in my neighbourhood, day or night; Violence is not a problem in my neighbourhood; My neighbourhood is safe from crime; My local neighbourhood is attractive; My neighbourhood offers many opportunities to be physically active; Local sports clubs and other facilities in my neighbourhood offer many opportunities to get exercise; Strange danger is a concern of mine; It is pleasant to walk in my neighbourhood; and, In my neighbourhood it is easy to walk to places. Two items examined social norms: I often see other people walking in my neighbourhood; and, I often see other people exercising in my neighbourhood [38]. Five items examined social trust and cohesion: People in this neighbourhood can be trusted; This is a close knit neighbourhood; People around here are willing to help their neighbours; People in this neighbourhood generally don’t get along with each other; and, People in this neighbourhood do not share the same values [39]. Additional items were based on concepts of social networks: I know many people in this neighbourhood; My child has many friends in this neighbourhood; and, There are not many other children around for my child to play with. Sense of community was also assessed with two items: This neighbourhood is a good place to live; and, This neighbourhood is a good place to raise children [40].

Items relating to adult’s park use, perceptions of parks, importance of park features for physical activity, and activity levels within parks are outlined in detail in Additional file 1: Table S1. Parent proxy-reported items on child’s park use, park satisfaction for children, child’s safety and independent mobility within the neighbourhood, and child’s time outdoors, physical activity and sedentary activities are detailed in Additional file 2: Table S2. Test-retest reliability of these items are also presented in these Tables. To examine test-retest reliability, 200 reliability surveys were mailed to residents in the Westerfolds area who had already returned a completed survey; 126 reliability surveys were returned (63% response rate). The reliability of the items were examined using one-way single measure intra-class correlation coefficient for continuous variables (ICC) and percent agreement for categorical variables. An ICC of ≥0.75 was considered excellent and 0.4-0.74 was considered good [41]. Percent agreement values were also calculated and were considered acceptable if above 66% [42]. Almost all items (95%, 42 of 44) had at least acceptable percent agreement and 93% of items (64 of 69) demonstrated good test-retest reliability (ICC ≥ 0.40). Overall, the test re-test reliability for the park-related items were acceptable for use at each of the time-points and for future studies.

### Translation

As a large proportion (14.2%) of residents within the City of Brimbank speak Vietnamese at home, the survey was also translated into Vietnamese. The survey was distributed to residents and school families surrounding Brimbank Park in English, accompanied by a letter written in Vietnamese stating that a copy of the survey in Vietnamese could be requested. Open-ended responses written in Vietnamese were translated in-house by a Vietnamese speaking research assistant.

#### Sample size calculations

Sample size calculations for the neighbourhood survey were based on ordered logistic regression analyses from a previous pilot natural experiment study in parks [32] by comparing responses for use of control and intervention parks post-refurbishment. This analysis yielded an estimated Odds Ratio (OR) across seven categories of frequency of park use (i.e. from ‘most days’ to ‘have not visited in the past 6 months’) of 4.74 [2.71, 8.33]. The proportional odds assumption was violated (p = .026), meaning that the OR at each category was not similar enough to summarise into one OR, therefore, generalised ordered logistic regression calculating six OR’s across seven categories was performed. Using a conservative approach, the smallest individual OR (1.41) was used in the following calculations. With alpha = 0.05 (two-tailed), beta = 0.20, this gives a required sample size of 444 at each time point [43] for both adults and children.

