#### Baseline response rate

From the 9649 surveys distributed, 1488 surveys were returned completed, with 866 surveys including data on children. A total of 4637 surveys were distributed via pre-schools and schools with 713 returned (15.4% response rate). A total of 4984 surveys were distributed via the two Councils with 772 returned (15.5% response rate) and 22.5% including responses about children. Twenty-eight Vietnamese surveys were requested; however, only three (11% response rate) were returned completed.

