## Discussion

The refurbishment of this large suburban park in a low SES area affords a unique opportunity to evaluate a ‘real world’ natural experiment. There is increasing interest in using the opportunities presented by natural experiments to generate evidence about population health impacts [47]. This study provides novel evidence for policy- and decision-makers regarding the role of parks for increasing community physical activity levels. Moreover, the location of the intervention park in a disadvantaged area will help inform the extent to which interventions of this type can beneficially influence the physical activity of those at higher risk in the population. Strengths of the study design include the wide range of comprehensive measures and the inclusion of partners which was integral to the data collection and will greatly assist the dissemination of results to key stakeholders. Previous research has suggested that building meaningful partnerships with diverse communities can improve health outcomes [48].

However, many challenges must be overcome in the development and implementation of this type of intervention study. One challenge of natural experiment research is timing the completion of measures with an unpredictable and frequently changing intervention timetable which is completely outside the researchers’ control [26]. The refurbishment works at Brimbank Park were delayed on numerous occasions, and significant negotiation and flexibility was required to co-ordinate the research funding availability with the intervention schedule. Typically, once grant money is awarded, data collection cannot be delayed indefinitely to accommodate delays in building works. Flexibility is therefore required by funding bodies to accommodate events outside of the researchers’ control.

An additional challenge is the ability to identify equally matched intervention and control parks. In the current study, it was not possible to match the parks according to area-level SES, hence the control park is located in a high SES neighbourhood and intervention park in a low SES area. However, given that the objective was to compare differences in changes in park use and in park-based physical activity between the intervention and control park, the study design will overcome this mismatch for area-level SES.

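### The survey's 444 is sized for one post-refurbishment comparison of two parks; for the stated objective, a difference in changes, it gives about 51% power at OR 1.41, not 80%

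*Protocol article*

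**What the plan says.** In the Protocol article, Sample size calculations (under Neighbourhood survey), the calculation starts from a pilot natural experiment, analysed "by comparing responses for use of control and intervention parks post-refurbishment". The outcome is ordinal, "across seven categories of frequency of park use". The pilot's summary OR was 4.74 (bracketed interval 2.71 to 8.33), but proportional odds was rejected (p = .026), so six separate ORs were fitted and "the smallest individual OR (1.41) was used in the following calculations". The result, for adults and for children alike, is: "With alpha = 0.05 (two-tailed), beta = 0.20" and a requirement of 444 at each time point. The text does not say whether 444 is per park or for both parks together.

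The Discussion gives the target as follows: "the objective was to compare differences in changes in park use and in park-based physical activity between the intervention and control park". It relies on this comparison of changes to deal with the control park lying in a high-SES area and the intervention park in a low-SES area. The Neighbourhood survey section plans repeated cross-sections at T1 and T3, not a cohort. Baseline response rate reports that "1488 surveys were returned completed, with 866 surveys including data on children".

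**The concern.** The contrast that was powered is not the contrast that the article says it will estimate. A comparison at one time has two independent groups. A difference in changes from repeated cross-sections has four (two parks, two waves), and no within-person correlation is designed in to recover precision. The stated beta of 0.20 therefore does not carry over.

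Falling back on the post-only comparison is not a way out, because the comparison of changes is the article's own answer to the SES mismatch. For the same reason, the article does not show that a post-only pilot OR of 1.41 represents an effect on change.

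At stake is how a null park-by-wave result in the survey would be read. It would pass as coming from an 80%-powered analysis. The gap matters most for children, at whom the play space is directed.

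**Working it through.** **Inputs from the article.** Two-sided alpha 0.05; power 80%; OR 1.41, so ln 1.41 = 0.3436; seven ordered categories; stated N = 444; T1 returns 1,488 (adults) and 866 (with child data).

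**Assumptions, not in the article.** Whitehead's proportional-odds approximation; the category constant c = 1 − Σp³, since no category proportions are given; equal split of returns by park (mailing was about equal, but returns by park are not reported); T1 returns repeated at T3; no school clustering.

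**Step 1: reproduce 444.** With (1.960 + 0.842)² = 7.849, the total for two equal groups is

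N = 12 × 7.849 / (0.3436² × c) = 798 / c.

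- c = 1 (mathematical limit): 798 in total, 399 per park.
- Seven equal categories (c = 0.980): 814 in total, 407 per park.
- c = 0.898: 888 in total, 444 per park.

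A second route, on the latent logistic scale with SD π/√3, gives 2 × 7.849 × 3.290 / 0.3436² ≈ 438 per park, within 2% of 444. Treating 1.41 as the OR of a single binary split needs at least 534 per park. So 444 is reproduced as a per-park figure for one two-park comparison. It cannot be a two-sided total, because the minimum total is 798.

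**Step 2: the difference in changes.** The log ratio of ORs is the difference of two independent log ORs, one per wave. With equal wave sizes its variance is the sum of two equal terms:

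SE(single) = √(12 / (N·c)); SE(change) = √(24 / (N·c)), with N the total per wave.

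Power = Φ(0.3436 / SE − 1.960).

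**Step 3: results at c = 0.898.**

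| N per wave, both parks | Contrast | SE | Power at 1.41 |
|---|---|---|---|
| 888 (444 per park) | single time | 0.1226 | 80% |
| 888 (444 per park) | difference in changes | 0.1734 | 51% |
| 1,488 (adult return) | difference in changes | 0.134 | 73% |
| 866 (child return) | difference in changes | 0.1756 | 50% |

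For 80% power at 1.41 the difference in changes needs 2 × 444 = 888 per park per wave, or 1,776 per wave. The latent-logistic route gives 875 per park per wave.

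**Step 4: sensitivity to c from 0.80 to 0.98.** 444 per park: 46–54%. Adults: 68–76%. Children: 46–53%. Even at c = 1 the figures are only 55%, 77% and 54%. No category distribution restores 80% at 1.41.

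**Step 5: minimum detectable ratio of ORs at 80% power,** exp(2.802 × SE):

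- 444 per park: exp(2.802 × 0.1734) = 1.63.
- Adults: exp(2.802 × 0.134) = 1.46.
- Children: exp(2.802 × 0.1756) = 1.64.

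**The case against.** The strongest reply is that 1.41 is the smallest of six category ORs and was chosen for caution, against a pilot summary of 4.74. On the formula above, a ratio of ORs of 1.8 already gives about 92% power with 444 per park, and 2.71, the lower end of the pilot interval, gives more than 99%. This stands as a limit on the consequence. It does not rescue the statement: the article sets the summary OR aside because proportional odds failed, and it attaches alpha and beta to 1.41.

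It can also be said that returns exceeded plan. For adults they did: 1,488 / 2 = 744 per park, which narrows the gap to 73% against 80%. For children they did not: 866 / 2 = 433 per park, just under 444.

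The percentages are less firm than they look. The constant 0.898 was picked because it reproduces 444, the method that the article cites is not visible, and the formula assumes proportional odds, which the pilot violated. This also stands. The part that does not depend on category proportions is the factor of two.

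A reader might infer three stronger claims that the article does not support:

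- That power could be as low as 29%, by taking 444 as the total for both parks. That reading cannot produce 444, so the figure should not be used. The missing unit is a wording matter.
- That objectives 1 and 2 as a whole are underpowered. The calculation covers the survey only. Park use and park-based activity are also measured by SOPARC, path monitors, traffic counters and intercept interviews, the last of which also record travel mode.
- That 1.41 is certainly contaminated by a pre-existing park difference. The article does not say whether the pilot model adjusted for baseline. It only fails to show that 1.41 is an effect on change.

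**Conclusion.** The point holds for the survey strand and at OR 1.41. The stated 80% power belongs to a single post-refurbishment comparison with about 444 per park. For the difference in changes that the Discussion names as the objective, the variance doubles and power is about 51%; about 888 per park per wave would be needed. At the T1 returns the shortfall is modest for adults (about 73%, range 68–76%) and larger for children (about 50%, range 46–53%).

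The doubling rests on independent cross-sections of similar size at the two waves. The percentages rest in addition on the Whitehead approximation with c = 0.898 (range 0.80–0.98), an even split by park, T1 returns repeated at T3, and no clustering; school clustering would be expected to lower them. It does not follow that the survey cannot detect effects of the size seen in the pilot.

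**What to change.** Reword the sample size paragraph so that it:

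- says that 444 is per park and applies only to a between-park comparison at a single time;
- gives, for the park-by-wave interaction at the T1 returns, the power at a ratio of ORs of 1.41 (about 73% adults, 50% children) and the minimum detectable ratio at 80% power (about 1.46 adults, 1.64 children), recalculated with the category proportions and returns by park observed at T1;
- notes that 1.41 comes from a post-only comparison and is used as a cautious working value, not as a demonstrated effect on change;
- confines the statement to the neighbourhood survey.

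The cost is one paragraph and a less favourable stated power. Recruitment, design and the target of estimation stay as they are.

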#### Baseline response rate

From the 9649 surveys distributed, 1488 surveys were returned completed, with 866 surveys including data on children. A total of 4637 surveys were distributed via pre-schools and schools with 713 returned (15.4% response rate). A total of 4984 surveys were distributed via the two Councils with 772 returned (15.5% response rate) and 22.5% including responses about children. Twenty-eight Vietnamese surveys were requested; however, only three (11% response rate) were returned completed.

#### Compensation

Each of the schools received a $75 book voucher as compensation for their time. All participants who returned a survey were included in a draw for one of two $500 gift vouchers.

### Direct observation of park users

To assess park usage and park-based physical activity, direct observations of park users was conducted at T1, and will be repeated at T2 and T3, using the SOPARC (the System for Observing Play and Recreation in Communities) [44]. This is a reliable instrument for assessing physical activity in community settings and recent studies have used SOPARC to specifically assess physical activity in parks [45,46]. This instrument is based on momentary time sampling and involves undertaking systematic observations (scans) of each participant within the park at a particular time.

At T1, at each park, six trained observers conducted observations of ten clearly defined target areas, which included the playground, walking/cycling paths, and open space areas. Target areas were pre-determined and comparable between the intervention and control parks and the same target areas will be targeted at T2 and T3. During each scan, observers recorded each individual within view in their target area according to: their broad age group (i.e. child (1-12 yrs), teen (13-20 yrs), adult (21-59 yrs), or older adult (60 yrs+); sex (male or female); and the activity they were engaged in (i.e. lying down, sitting; standing; moderate; or vigorous activity). During weekdays, observations were conducted every hour from 7:30 am to 4:30 pm (except for one day where observations concluded at 1:30 pm due to rain), and on weekend days every hour from 8:30 am to 4:30 pm. Data were collected for a total of eight days, including four weekdays and four weekend days. This equated to a total of 1460 scans across the two parks. Scheduling of daily observations was consistent between the intervention and control parks and observations were not conducted on days of forecasted rain.

### Park user intercept interviews

Face-to-face intercept interviews were completed at T1, and will be repeated at T2 and T3 with English-speaking adult park users on days when observations are conducted. The items included in this short (5–10 minute) interview are outlined in Table 1.

**Table 1 T1:** Variables assessed in the intercept survey

**Socio-demographic variables**	**Response options**
Age	Years
Sex	Male/Female
Suburb of residence	Open ended
Time living at current address	Years
Do you own a dog?	Yes/No
Do you have a child <2 years?	Yes/No
Do you have a child 2–15 years?	Yes/No
**Park use**	
What is your main reason for visiting the park today?	1) walk, 2) walk the dog, 3) jog, 4) ride a bike, 5) ball games, 6) exercise, 7) supervise children, 8) take children to playground, 9) relax, 10) picnic, 11) socialise, 12) attend major event/celebration, 13) visit café, 14) view nature, 15) other
Why did you visit this park instead of other parks?	Open ended
How long do you plan to stay in the park today?	1) <30 mins, 2) 30 mins-1 hr, 3) 1 < 2 hrs, 4) 2 < 3 hrs, 5) 3 < 4 hrs, 6) 4+ hrs
Who came with you to the park today?	1) alone, 2) partner, 3) child(ren), 4) grandchildren, 5) friends, 6) organised group, 7) dog, 8) other
How did you get to this park today?	1) walked, 2) cycled, 3) public transport, 4) car, 5) jogged, 6) other
Did you come to the park from your home?	Yes/No
How long did it take for you to get to this park today?	Minutes
In the past 3 months, on average, how often have you visited this park?	1) daily, 2) 2–3 times per week, 3) once per week, 4) 2–3 times per month, 5) once per month, 6) < once per month, 7) first time to this park
In the past 3 months, which describes your usual activity levels during your visits to this park?	1) mostly sitting, 2) mostly light activities, 3) mostly moderate activities, 4) mostly vigorous activities
What could be done to encourage you to visit this park more often?	Open ended

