**Child variables***	
Age	Years
Sex	Male/Female
Are they with you in the park today?	Yes/No
Have they ever visited this park?	Yes/No
In the past 3 months, on average, how often have they visited this park?	1) daily, 2) 2–3 times per week, 3) once per week, 4) 2–3 times per month, 5) once per month, 6) < once per month, 7) first time to this park
What do they usually do when at this park?	Open ended
Who do they usually come with to this park?	1) alone, 2) adult, 3) friends, 4) organised group, 5) dog, 6) other

*Proxy-reported by adult for child aged 2–15 years who has the next birthday.

At T1, trained, clearly identifiable research assistants approached park users in the specified target areas, explained the study and all ethical considerations, and invited participation. Participants were also asked if they had a child(ren) aged 2–15 years, and if so, they were asked to consider the child in the age range who had the next birthday and answer additional questions relating to this child’s use of the park. Overall, 794 park users agreed to participate (75.3% of those approached, excluding those who had already completed an interview). A total of 313 interviews were conducted at the intervention park (73.6% of those approached) and 481 interviews at the control park (76.5% of those approached). The child questions were completed by 366 (46.1%) participants overall. The main reasons for non-participation apart from already having completed the survey (44%) included: too busy/no time (21%), did not want to stop exercising (8%), were not interested (6%) and/or did not speak English (4%).

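### The intercept interview's visit-frequency item has no option for 4–6 visits a week, so the split between its top two categories is unreliable for adults and children

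*Protocol article*

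**What the plan says.** The item is in Table 1 of the protocol article. Under 'Park use', adults are asked "In the past 3 months, on average, how often have you visited this park" and the options begin "1) daily, 2) 2–3 times per week, 3) once per week, 4) 2–3 times per month", followed by a fifth for monthly visits, a sixth for rarer visits and a seventh for people on their first visit. Under 'Child variables', the adult is asked about the child, "In the past 3 months, on average, how often have they visited this park", and the same seven options are printed beside the question.

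Neither list has an 'other' option, although the items on main reason for visiting, companions and mode of travel in the same table do. The article gives no rule for coding an answer that falls between two options.

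The instrument is meant to be reused: "Face-to-face intercept interviews were completed at T1, and will be repeated at T2 and T3 with English-speaking adult park users". At T1, "Overall, 794 park users agreed to participate (75.3% of those approached, excluding those who had already completed an interview". Of these, 313 were at the intervention park and 481 at the control park. The child questions were completed by 366.

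**The concern.** A closed frequency item should give every plausible answer exactly one place. This one does not. Someone who comes on most weekdays, or four times in a typical week, has no correct option. The respondent or the interviewer has to choose between one option that is too high and one that is too low, or skip the item.

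The gap lies at the regular-user end. Interviews take place in the park, so a person's chance of being met rises with how often he or she comes. Walking, dog walking, jogging and cycling are all listed reasons for a visit, which makes a 4–6 visits pattern believable. What is at stake is the meaning of the top category. A rise or fall in the share of daily visitors could reflect how in-between answers were placed. A real move from two or three visits a week to five could be missed, or could appear as a move to daily use.

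**Working it through.** The article gives no sample size or power figure for this item, so none has to be reproduced. The check is whether each whole number of visits per week has a printed option.

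**Inputs.** The seven options in Table 1 (adult and child lists are identical), the three-month recall period in both questions, and the T1 counts under Table 1. Three months is taken as 13 weeks.

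**T1 counts.** 313 + 481 = 794, and 366/794 = 0.461, or 46.1%. Both agree with the article.

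**Mapping.** Visits in the recall period = visits per week × 13.

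| Visits per week | Visits in 13 weeks | Printed option | After merging options 1 and 2 |
|---|---|---|---|
| 1 | 13 | 3 | 3 |
| 2 | 26 | 2 | merged |
| 3 | 39 | 2 | merged |
| 4 | 52 | none | merged |
| 5 | 65 | none | merged |
| 6 | 78 | none | merged |
| 7 | 91 | 1 | merged |

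Three of the seven values have no option. The list passes directly from 39 visits to 91, and everyone between 52 and 78 falls in the gap. Smaller gaps exist lower down, for example between option 4 and option 3, but none of them skips a whole number of visits per week.

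**Does merging cure it?** A 4–6 visitor recorded at T1 as option 1 is in the merged category. So is one recorded as option 2. The merged category therefore does not depend on how the T1 answer was placed. The exception is an answer left blank, which stays missing.

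**Does a new code at T2 and T3 cure it?** With a 4–6 option added, each value from 1 to 7 maps to exactly one option. The new code folds into the merged category, so comparability with T1 is kept.

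**How many respondents?** This cannot be computed. Purely as an assumption, if 5% to 15% of the 794 adults at T1 visited 4–6 times a week, the number would be 0.05 × 794 ≈ 40 to 0.15 × 794 ≈ 119. Nothing in the article supports a particular value in that range or confines the share to it.

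**The case against.** The strongest reply accepts the gap and disputes its importance.

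- **The item is one descriptor among many.** The article does not name it as a primary outcome. Park usage is also measured by direct observation, path and vehicle counters and the neighbourhood survey, and the sample size rests on the survey. This stands. A reader might infer that the trial's park-use outcome is misclassified, but the documents support that only for the intercept frequency measure.
- **The same list serves both parks and all waves, and trained staff administer it.** If in-between answers are always handled alike, resolution is lost but no between-park difference in change need arise, and the rank order of categories is kept. This stands as far as bias goes: different handling between waves or parks is possible but not shown. It does not remove the fault. An interviewer manual, which an article may well omit, could only settle which of two wrong options is used.
- **The share affected is unknown.** This stands. Half of the observation days were weekend days, people already interviewed were not counted again, and no frequency distribution is reported.
- **Merging categories is an analysis matter.** This stands in part. The plan for the analysis may be elsewhere, but the response list itself is fixed in the article.

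Two further inferences are tempting and should not be drawn. One is that the interview cannot be aligned with the neighbourhood survey because the scale in the sample size section runs "from ‘most days’ to ‘have not visited in the past 6 months". That scale is described there as coming from an earlier pilot study. The present survey's own items are in an additional file not shown, and the article does not propose to align the two instruments. The other is to convert the categories to weekly visits and quote a percentage over- or understatement. The article plans no such conversion, so those percentages would not be effects on any result.

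**Conclusion.** The fault is certain and its reach is limited. As printed, the adult and child visit-frequency items are not exhaustive: 4–6 visits a week has no valid answer, and the boundary between options 1 and 2 cannot be trusted. The existence of the gap needs no assumption beyond reading the table as it stands. Its effect on any result cannot be sized, because it depends on how many users visit 4–6 times a week and on how their answers were placed, and the article reports neither. This is a small but real instrument fault that can be repaired cheaply while T2 and T3 are still ahead.

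**What to change.** 1. In every comparison that includes T1, merge options 1 and 2 into a single category of two or more visits per week, for the adult and the child item alike.
2. Draw no conclusion from a change in the daily category alone.
3. At T2 and T3, add a code for 4–6 visits per week to both items and state that it folds into the merged category. This gives finer detail for T2–T3 comparisons only and adds nothing to comparisons with T1.

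The cost is one extra response code and one recoding line. The downsides are less detail at the top of the scale in comparisons with T1, and a small change to a repeated instrument after baseline.
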